### Ethical Considerations

This study will be conducted in accordance with the Declaration of Helsinki and Good Clinical Practice guidelines. Ethics approval has been granted by the Research and Ethics Committee of the Universiti Kebangsaan Malaysia (RECUKM; the National University of Malaysia; study ID UKM PPI/111/8/JEP-2023-596). All participants will provide informed consent before participating, and their privacy will be kept confidential.

The study findings will be disseminated through publication in peer-reviewed journals and presentations at national and international congresses. A summary of the trial results will also be made available on the Australian New Zealand Clinical Trials Registry database. All necessary regulatory approvals for the study have been obtained. Upon trial completion, participants will receive personalized feedback regarding their involvement and the study outcomes.

## Results

Funding for this study from RECUKM began in November 2023. Between January 2023 and May 2023, we drafted the initial ethics proposal and hired the research staff. Research ethics applications were submitted to the RECUKM from May 2023 to November 2023. We anticipate publishing the study results in 2025.

This study will evaluate the effectiveness of CIMT combined with NMES, CIMT alone, and conventional neurodevelopmental therapy in rehabilitating UE function in chronic stroke survivors. The findings could enable physiotherapists to develop innovative therapies to promote UE function and assist in identifying the most effective treatments for poststroke UE dysfunction. We hypothesize that CIMT combined with NMES will be more effective than the other 2 therapies in improving UE function among survivors of stroke.

## Discussion

### Anticipated Findings

This study evaluates the effects of combining CIMT with NMES on UE function among chronic stroke survivors. We hypothesize that the combined CIMT+NMES intervention will produce superior improvements in motor function and perceived functional use compared to CIMT alone or conventional therapy. This dual approach leverages complementary mechanisms: CIMT addresses learned nonuse through intensive task practice [48], while the NMES facilitates muscle activation and enhances proprioceptive feedback to support voluntary movement.

We examined current rehabilitation paradigms for chronic stroke to contextualize our approach within existing evidence. CIMT has established efficacy for improving UE function in selected populations of individuals who have experienced a stroke through forced use and mass practice tasks [49]. Similarly, NMES demonstrates clear benefits for muscle strengthening and motor unit recruitment in paretic limbs [50]. However, a few studies have investigated their combined therapeutic potential [10]. Recent evidence indicates that multimodal rehabilitation approaches may amplify neuroplastic changes through synergistic cortical reorganization mechanisms. Functional magnetic resonance imaging studies have documented enhanced cortical activation patterns when peripheral electrical stimulation accompanies intensive motor training, suggesting accelerated neural adaptation compared to single interventions [21].

This study advances this emerging field by providing the first systematic comparison of combined CIMT+NMES therapy against established monotherapies. This investigation addresses a critical gap in stroke rehabilitation evidence, particularly for chronic stroke survivors who typically experience limited recovery with conventional approaches. By examining whether combined interventions overcome the ceiling effects often observed with single modalities, our findings will inform evidence-based treatment selection for this challenging population.

### Strengths and Limitations

This trial incorporates several methodological strengths that enhance scientific rigor and clinical applicability. Blinded outcome assessors evaluate all participants using validated instruments spanning the International Classification of Functioning, Disability, and Health framework, ensuring a comprehensive assessment of motor impairment, activity limitations, and participation restrictions. Our standardized intervention protocols, supported by detailed treatment manuals and competency-based therapist training, promote consistent implementation across sites. The pragmatic trial design, conducted within existing rehabilitation centers using available clinical resources, enhances external validity and facilitates future implementation.

We acknowledge specific limitations inherent in our study design. While pragmatically necessary given resource constraints, the single-cluster-per-arm randomization strategy prevents traditional design effect calculations in our sample size calculation. We have addressed this limitation through conservative effect size selection and comprehensive statistical modeling that includes the center as a fixed effect covariate. Our mixed ANOVA approach protects against type I error inflation while maintaining adequate sensitivity for detecting clinically meaningful differences. The absence of long-term follow-up assessments limits our understanding of treatment durability; however, immediate postintervention outcomes will establish the foundation for future longitudinal investigations.

Despite rigorous standardization procedures, therapist-delivered interventions inevitably introduce some variability. We minimize this concern through mandatory competency assessments and structured fidelity monitoring. These mitigation strategies ensure that observed treatment differences reflect intervention efficacy rather than health care provider variability.

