### Recruitment and Randomization

Participants will be recruited from the NASAM. Three NASAM centers will be randomly assigned to 1 of 3 groups: the CIMT combined with the NMES group, the CIMT-only group, or the control group. Due to the specific nature of the therapies and the distinct characteristics of the centers, randomizing individual participants within centers is impractical. A cluster randomization approach will be used to minimize contamination among patients attending the same center. In addition, to minimize the risk of contamination between intervention groups, a cluster randomization approach will be used, wherein health care centers will serve as the unit of randomization. Each participating center will be randomly allocated to 1 of the 3 intervention arms using a computer-generated sequence administered by research personnel not involved in intervention delivery or outcome assessment. This concealed allocation process ensures allocation concealment and methodological rigor. Following randomization, all eligible patients who have experienced a stroke attending a given center will receive only the intervention protocol assigned to that facility. This methodological approach enables consistent intervention delivery within each site while substantially reducing the likelihood of cross-contamination between intervention groups—a critical consideration when evaluating health care provider–delivered rehabilitation protocols with behavioral components.

Eligible participants will provide written informed consent before their involvement in the study. The principal investigator or a trained research staff member not involved in therapy delivery will be responsible for obtaining consent from each participant. This process will take place only after participants have received a comprehensive explanation of the study procedures, ensuring that they clearly understand their involvement and the associated risks and benefits.

Following the informed consent process, baseline demographic information, including the participants’ names, ages, and gender, will be collected. Once demographic data have been obtained, the remaining baseline assessments will be conducted. Throughout the study, the confidentiality of all participants’ personal information and data will be strictly maintained in accordance with established research ethics guidelines and data protection regulations.

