### Sample Size Calculation

We used the G*Power software (version 3.0.10; University of Düsseldorf) to calculate the required sample size. A mixed model ANOVA, a statistical method used to analyze the effects of interventions over time and between groups, was selected to analyze the interventions’ time, group, and interaction effects. The *F* test (ANOVA repeated measures within and between interactions), a specific type of statistical test used in the mixed model ANOVA, was selected for this analysis. With a study power of 80%, an α level of .05, and an effect size of 0.25 (based on the primary outcomes from a previous CIMT study [47]), a minimum sample size of 42 participants (14 in each group) is required. If a group has more than 14 eligible participants, the first 14 to provide consent will be recruited based on the referral date. This first-come, first-served approach ensures transparency in participant selection while maintaining cluster integrity.

An intention-to-treat analysis, which includes all randomized participants, regardless of their adherence to the protocol or completion of the study, will be implemented for this RCT. Under this approach, all recruited participants will be included in the final analysis regardless of protocol adherence, withdrawal, or discontinuation. For participants who withdraw or discontinue the treatment, their baseline data will be used as exit data in the primary analysis. This conservative approach acknowledges the potential impact of missing data while maintaining randomization integrity. Sensitivity analyses using multiple imputation techniques, which are statistical methods used to handle missing data, will be conducted to assess the robustness of findings against different missing data assumptions. This analytical strategy aligns with CONSORT guidelines for reporting randomized trials and addresses potential selection bias that might occur with complete-case analysis.

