### Conclusions

This protocol addresses a critical gap in stroke rehabilitation evidence through rigorous evaluation of combined therapeutic approaches, integrating CIMT with NMES to target both voluntary movement control and direct muscle activation through complementary neuroplastic mechanisms. By systematically examining whether multimodal interventions produce synergistic effects exceeding those of single treatments, our study advances rehabilitation science through a comprehensive methodological framework that incorporates standardized protocols, quantitative fidelity monitoring, and cluster-appropriate statistical modeling, ensuring reliable evidence generation for clinical practice guidelines. Beyond establishing comparative efficacy, this research will elucidate optimal dosing parameters and practical implementation strategies for complex rehabilitation interventions, enabling clinicians to make informed decisions about resource allocation and treatment selection for chronic stroke survivors while contributing essential evidence toward developing personalized, evidence-based rehabilitation strategies that maximize functional recovery in this underserved population.

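### With one center per arm, neither the mixed ANOVA nor a fixed center effect controls the type I error of the arm comparison, although the protocol says the ANOVA does

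*Protocol article*

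**What the plan says.** Under Recruitment and Randomization: "Three NASAM centers will be randomly assigned to 1 of 3 groups", "wherein health care centers will serve as the unit of randomization". Table 2 confirms one center per arm. Therapist Training and Standardization adds that one therapist treats everyone at a center. The Statistical Analysis section plans a two-way mixed ANOVA at P<.05, with baseline motor function and stroke severity as possible covariates. It also plans linear mixed models with center as a fixed covariate and random intercepts for participants only. It says no design effect is needed and that inference on the group-by-time interaction remains valid.

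Strengths and Limitations concedes that "the single-cluster-per-arm randomization strategy prevents traditional design effect calculations in our sample size calculation". It then says this has been addressed by a conservative effect size and by the fixed center covariate, and continues: "Our mixed ANOVA approach protects against type I error inflation while maintaining adequate sensitivity for detecting clinically meaningful differences". On therapist differences it adds: "These mitigation strategies ensure that observed treatment differences reflect intervention efficacy rather than health care provider variability". The Conclusions describe the modeling as suited to clusters, "ensuring reliable evidence generation for clinical practice guidelines".

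**The concern.** In a cluster trial, the arm effect has to be judged against variation between clusters. Here there is one cluster per arm, so that variation cannot be estimated and the planned tests set it to zero. The protocol gives a reason to doubt zero: it justifies cluster randomization partly by "the distinct characteristics of the centers".

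Center and arm coincide exactly, and therapist too by the training section. A P value below .05 could therefore come from a modest difference between three sites or three therapists, yet would be reported as comparative efficacy. This affects every between-arm conclusion, and no later analysis plan can repair it. The information is absent from the design.

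**Working it through.** **Inputs.** From the protocol: 3 centers and 3 arms, center as the unit of randomization, 14 participants per center (42 in all), two assessments (baseline and postintervention), and "With a study power of 80%, an α level of .05, and an effect size of 0.25" for the within-between interaction. Assumed because not stated: a repeated-measures correlation of 0.5 and the ICC of the change score, r.

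**1. The plan's own figure.** With f = 0.25, N = 42, m = 2 time points and correlation 0.5:
- Noncentrality is f² × N × m / (1 − 0.5) = 0.0625 × 42 × 2 / 0.5 = 10.5, on df 2 and 39.
- The critical F is 3.238 and power is 0.803. N = 39 gives 0.769.
- So 42 reproduces. It treats the 42 participants as independent.
- At correlations of 0.3 and 0.7 the same N gives 0.65 and 0.96.

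**2. Degrees of freedom between centers.** 3 centers − 3 arms = 0.

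**3. The fixed center covariate.** A design matrix with an intercept, two arm columns and two center columns has 5 columns and rank 3, the same as with arm alone. Center is either dropped or takes the place of arm.

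**4. Type I error of the group-by-time test.** With two time points this test is a one-way ANOVA on change scores. Let σc² be the between-center and σe² the within-center variance of change, so σc²/σe² = r/(1 − r). With no treatment effect, the between-arm mean square has expectation σe² + 14σc² and the error mean square σe². With normal center effects, F is therefore distributed as k × F(2,39), where k = 1 + 14r/(1 − r). The true error rate is P[F(2,39) > 3.238/k].

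| Assumed r | k | True error rate | SE multiplier √k |
|---|---|---|---|
| 0 | 1.000 | 5.0% | 1.00 |
| 0.001 | 1.014 | 5.2% | 1.01 |
| 0.005 | 1.070 | 6.0% | 1.03 |
| 0.01 | 1.141 | 7.1% | 1.07 |
| 0.02 | 1.286 | 9.4% | 1.13 |
| 0.05 | 1.737 | 16.9% | 1.32 |
| 0.10 | 2.556 | 29.3% | 1.60 |

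Simulation with 60,000 trials per setting gave 7.0%, 16.9% and 29.2% at r = 0.01, 0.05 and 0.10.

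**5. A center shift constant over time.** Here the ICC refers to a single time point, with correlation 0.5. Simulated rejection rates under the null at ICC 0.05 and 0.10:
- unadjusted interaction: 4.8% and 5.2% (no inflation);
- group main effect: 20.7% and 35.5%;
- baseline-adjusted comparison: 8.2% and 12.0%.

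**6. Power.** Total change-score variance is held fixed, so noncentrality becomes 10.5/(1 + 13r).
- Test as planned, critical value 3.238 unchanged: the rejection rate stays at 0.79 to 0.80 for r from 0 to 0.10 (0.77 to 0.80 if within-center variance is held fixed instead).
- Critical value raised to k × 3.238, which requires a known ICC: noncentrality is 9.29, 6.36 and 4.57, and power is about 0.75, 0.58 and 0.44, at r = 0.01, 0.05 and 0.10.

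**The case against.** Several points on the other side are fair.

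- **The limitation is disclosed.** Strengths and Limitations names the single cluster per arm, and Future Directions leaves definitive estimates to larger trials. That stands, but the same section then declares the problem addressed, and the Statistical Analysis section claims valid inference. Disclosure followed by a wrong reassurance does not inform the reader.
- **Center variance may be small.** Standardized training, fidelity audits and a single traveling assessor are meant to reduce it. At r = 0.001 or 0.005 the error is only 5.2% or 6.0%. That stands as a statement about size. But these measures cannot be shown to bring the variance to zero, and this trial cannot estimate it.
- **Effect size choice.** A conservative effect size influences N and power. It has no bearing on type I error.

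Two stronger readings are tempting and not supported. A reader might infer that every non-zero center effect inflates the test on which the trial was sized. It does not: a shift constant over time cancels from the unadjusted interaction, and the center characteristics that the protocol mentions are not shown to affect change. A reader might also infer that the planned test loses its 80% chance of rejection once the ICC is above zero. Its rejection rate hardly moves. What fails is its validity as a 5% test, and power falls only once that level is restored.

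**Conclusion.** The claim of protection against type I error inflation is wrong as written, and so is the claim of valid inference for the interaction. This rests on the design alone: 0 df between centers, and center aliased with arm. The size depends on an ICC that the document does not give. Over assumed change-score ICCs of 0.001 to 0.10, the nominal 5% group-by-time test has a true error rate of 5.2% to 29.3%. Normal center effects and 14 participants per center are assumed. It exceeds 5% for any positive variance between centers in change. Center shifts constant over time leave that test intact but affect the group main effect and baseline-adjusted comparisons. The assurance that differences reflect efficacy rather than the provider cannot be supported by these data. The error must be corrected because it bears on every comparison between arms.

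**What to change.** 1. Delete the type I error sentence and the sentence attributing observed differences to efficacy from Strengths and Limitations. Delete the valid-inference sentence from Statistical Analysis.
2. Drop center as a covariate beside arm, and state that arm, center and therapist effects cannot be separated in this design.
3. Report arm differences with confidence intervals under pre-stated change-score ICCs of 0, 0.01, 0.05 and 0.10, with standard errors multiplied by 1.00, 1.07, 1.32 and 1.60. Label every P value for an arm comparison as conditional on no center effect.
4. In Sample Size Calculation, state that 80% power at a valid 5% level assumes no center variance in change and a repeated-measures correlation of about 0.5. Give the corrected-level figures (about 0.75, 0.58 and 0.44) for context.
5. Describe the trial as an exploratory three-center comparison and soften the claim in the Conclusions about evidence for guidelines.

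The cost is wording and one sensitivity table, with no added participants or centers. The downside is weaker claims. Estimating variance between centers would need more than one center in at least one arm, which is a different trial.

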### Clinical Implications and Future Directions

Our findings will directly inform clinical decision-making regarding optimal rehabilitation strategies for chronic stroke survivors with persistent UE deficits. Should the combined intervention demonstrate superiority, clinicians will gain evidence supporting integrated treatment protocols that maximize functional recovery potential. The comprehensive outcome battery, including motor function (FMA-UE), activity performance (Wolf Motor Function Test), perceived use (Motor Activity Log), and self-efficacy (UPSET), provides multidimensional insights into treatment effects across the International Classification of Functioning, Disability, and Health domains.

Future research should expand upon our foundation through several critical avenues. Large-scale multicenter trials incorporating cluster randomization with appropriate design effects will establish definitive efficacy estimates. Extended follow-up periods of 6 to 12 months will determine whether initial gains translate into sustained functional improvements. Neurophysiological assessments, including transcranial magnetic stimulation and electroencephalography, could elucidate the cortical mechanisms underlying potential synergistic effects [51].

### Dissemination Plan

We have developed a comprehensive dissemination strategy to ensure rapid translation of findings into clinical practice. Primary dissemination will occur through publication in high-impact rehabilitation journals with open-access options to maximize accessibility. Conference presentations at international forums will facilitate direct engagement with clinical and research communities.

To accelerate clinical implementation, we will develop practitioner-oriented resources, including evidence summaries, clinical decision algorithms, and video training modules demonstrating proper technique. Collaboration with professional organizations will support integration into clinical practice guidelines and continuing education curricula. Patient-centered knowledge translation activities include creating accessible educational materials explaining treatment options and expected outcomes, available in multiple languages to serve diverse populations. Partnerships with stroke survivor organizations will ensure broad distribution through established communication channels, empowering patients to advocate for evidence-based care.

### Conclusions

This protocol addresses a critical gap in stroke rehabilitation evidence through rigorous evaluation of combined therapeutic approaches, integrating CIMT with NMES to target both voluntary movement control and direct muscle activation through complementary neuroplastic mechanisms. By systematically examining whether multimodal interventions produce synergistic effects exceeding those of single treatments, our study advances rehabilitation science through a comprehensive methodological framework that incorporates standardized protocols, quantitative fidelity monitoring, and cluster-appropriate statistical modeling, ensuring reliable evidence generation for clinical practice guidelines. Beyond establishing comparative efficacy, this research will elucidate optimal dosing parameters and practical implementation strategies for complex rehabilitation interventions, enabling clinicians to make informed decisions about resource allocation and treatment selection for chronic stroke survivors while contributing essential evidence toward developing personalized, evidence-based rehabilitation strategies that maximize functional recovery in this underserved population.

## Appendix

Multimedia Appendix 1 SPIRIT (Standard Protocol Items: Recommendations for Interventional Trials) checklist.

## Abbreviations

CIMT: constraint-induced movement therapy
CONSORT: Consolidated Standards of Reporting Trials
FMA-UE: Fugl-Meyer Assessment for upper extremity
NASAM: National Stroke Association of Malaysia
NMES: neuromuscular electrical stimulation
RCT: randomized controlled trial
RECUKM: Research and Ethics Committee of the Universiti Kebangsaan Malaysia
UE: upper extremity
UPSET: Upper Limb Self-Efficacy Test
